**Methods:**

This is a randomized controlled trial involving adults aged 18 to 75 years from the counties of l’Anoia and Bages (Catalonia, Spain) who meet the Rome IV diagnostic criteria for chronic constipation. A total of 45 participants will be randomly assigned in a 1:1:1 ratio (approximately 22‐23 per center, with 15 per group overall) into 3 groups: a control group, behavioral intervention (BI) group, and behavioral intervention and massage (BIM) group. All participants will complete baseline assessments that include the Rome IV criteria, the Bristol Stool Form Scale, the CVE-20 quality of life questionnaire, and the International Physical Activity Questionnaire. The BI group will receive 2 group education sessions, focused on healthy bowel habits, diet, hydration, physical activity, stress management, and medication use, delivered by a multidisciplinary team. The BIM group will receive the same intervention as the BI group, plus two 30-minute sessions with a physiotherapist to learn abdominal self-massage techniques. The control group will receive usual care. Follow-up assessments will occur at 3 and 6 months after the intervention using the same instruments and a self-recorded calendar of laxative use and massage application. Data will be analyzed using appropriate statistical tests, including the *χ*^2^ test, a 2-tailed *t* test, and ANOVA/Kruskal-Wallis tests, depending on variable type.

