### Sample and Randomization

Calculations were based on published evidence suggesting that approximately 90% of patients in the control group would remain constipated at 3 months. We hypothesized that this proportion would decrease to 40% in the intervention groups (BI and BIM), corresponding to a 50% absolute difference. To detect this difference with 80% power and a 2-sided significance level of 5%, while allowing for a 10% dropout rate, 15 participants per group are required. With 3 groups, the total sample size will therefore be 45 participants in total. Recruitment will take place across the 2 participating centers (Anoia and Bages), with approximately 7 to 8 participants per group expected to be recruited at each center.

The sample will be selected (1) by means of a medical history review by nursing or medical personnel; if the health professional considers that the patient meets the criteria, they will refer the patient to the research physiotherapist; and (2) indirectly, by putting up posters in *casals cívics* (civic facilities) and pharmacies in the city. Anyone learning about the study this way can make an appointment with their health professional of reference (ie, nursing or medical staff) and discuss their interest in participating in the study. If the health care professional confirms that the patient meets the criteria, they will refer the patient to the research physiotherapist.

The randomization and allocation of patients will be performed by simple randomization using the specialized software RStudio (version 4.2.1; R Foundation for Statistical Computing). The distribution is expected to be homogeneous between groups. Randomization will be conducted by an independent researcher, and allocation will be concealed using sequentially numbered, opaque, sealed envelopes prepared in advance. This procedure ensures allocation concealment and minimizes selection bias.

The chosen sample size is based on feasibility and resource availability and is sufficient to detect large effect sizes. This study aims to assess the feasibility and potential impact of the intervention and to provide effect size estimates to guide future large-scale trials.

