### Variables

We will evaluate a set of indicators on constipation and other patient characteristics, as shown in Table 1. Outcomes will be assessed individually and at 5 different time points: before starting the intervention, on the same day of the intervention, 3 months after the intervention, 6 months after the intervention, and 12 months after the intervention. Data will be collected through standardized questionnaires to be completed independently by the participants.

**Table 1. T1:** Study variables.

Study area and instrument		Measurement time point
Constipation		
	Rome IV criteria—degree of constipation	Tpre^a^, T0^b^, T3^c^, T6^d^, T12^e^
	Bristol Stool Form Scale—stool type	T0, T3, T6, T12
Quality of life		
	CVE-20 questionnaire	T0, T3, T6, T12
Use of laxatives		
	Self-recorded calendar of laxative intake	T3, T6, T12
Patient characteristics		
	ECAP^f^—sex, age, previous conditions	Tpre
	IPAQ^g^—physical activity level	T0, T3, T6, T12
Habit change intention		
	Dichotomous question	T0

a Tpre: before the intervention.

b T0: start of the intervention.

c T3: 3 months after the intervention.

d T6: 6 months after the intervention.

e T12: 12 months after the intervention.

f ECAP: Electronic Primary Care Clinical Workstation.

g IPAQ: International Questionnaire of Physical Activity.

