### Statistical Analysis

The main variable will be the percentage of patients with constipation 3 and 6 months after the start of treatment for each group, a dichotomous qualitative variable. Prevalence will be estimated and analyzed using the *χ*^2^ test.

The other variables will be reported as percentages and counts for categorical variables and through mean, median, deviation, and quartiles for continuous variables. In order to analyze relationships between the main variable and the sociodemographic or other explanatory variables, the *χ*^2^ test will be used, and the relative risk will be estimated to compare the reduction between the two intervention groups with respect to the control group.

To evaluate the secondary variable, a continuous quantitative variable, ANOVA or the Kruskal-Wallis test will be used to determine differences between the 3 groups. To determine differences between pairs of groups, the Student *t* test or Mann-Whitney test will be used. Analyses will use 95% CIs, and the significance level will be set at 5%.

Due to the nature of the intervention, participant blinding is not feasible. However, to minimize potential bias in outcome assessment, data entry and statistical analysis will be performed by a researcher who is blinded to group allocation. This approach ensures objectivity in the interpretation of results, particularly for subjective outcome measures. All analyses will follow the intention-to-treat principle, including all randomized participants in the groups to which they were originally assigned. Missing data will be handled using multiple imputation under the assumption that data are missing at random. Statistical analysis will be performed with RStudio.

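### One χ² test for every explanatory variable makes age a set of unspecified categories and leaves arm unadjusted, which costs power in an exploratory analysis

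*Protocol article*

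**What the plan says.** The Statistical Analysis section of the protocol article defines the main variable as constipated or not at 3 and 6 months. For its relation to patient characteristics it states: "In order to analyze relationships between the main variable and the sociodemographic or other explanatory variables, the *χ*^2^ test will be used". The sentence then turns to relative risks for the two intervention groups against control.

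Table 1 (Variables section) lists the patient characteristics as "ECAP^f^—sex, age, previous conditions" and "IPAQ^g^—physical activity level", and adds a yes/no question on the intention to change habits. Age may run from 18 to 75 (Population section). The article does not say whether the IPAQ is used as a numeric score or as ordered levels.

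The Statistical Analysis section reserves ANOVA, Kruskal-Wallis, *t* and Mann-Whitney tests for comparing groups on the secondary, continuous variable. The abstract's Methods paragraph is more general and ends its list of tests with "ANOVA/Kruskal-Wallis tests, depending on variable type".

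The Sample and Randomization section assumes that "approximately 90% of patients in the control group would remain constipated at 3 months" and that the figure is 40% in both intervention groups.

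**The concern.** A χ² test works on a cross-table, so a numeric variable such as age has to be grouped before it can be used. The article gives neither cut-points nor a reason for grouping. Grouping discards information that has already been collected, and cut-points left open can be chosen after the data are seen.

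A two-way table of outcome by characteristic also has no term for arm, which by the plan's own assumption is a very strong determinant of the outcome. Leaving it out makes the association with any other variable harder to detect.

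At stake is whether a real predictor of persistent constipation is missed and reported as showing no association. The trial has 45 participants and little information to spare.

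**Working it through.** **Inputs from the article.** Constipation rates 90% (control), 40% (BI) and 40% (BIM); 80% power; two-sided 5%; 10% dropout; 15 per group (Sample and Randomization).

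**The plan's own figure.** With p₁ = 0.90, p₂ = 0.40 and mean 0.65:

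n = [1.96·√(2·0.65·0.35) + 0.842·√(0.90·0.10 + 0.40·0.60)]² / 0.50² = 13.04 per group; 13.04 / 0.9 = 14.5, rounded up to 15.

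The stated 15 per group is reproduced. It is the basis for the between-arm comparison and says nothing about explanatory variables.

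**Inputs assumed.** The article gives no effect size for any explanatory variable. Assumed here: a normally distributed baseline variable, linear on the logit scale, with an odds ratio (OR) per standard deviation of 2.0, 2.5 or 3.0. Dropout of 10% leaves 15 × 0.9 = 13.5 per arm; 14 per arm (42 in all) was used.

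**Pooled over arms.** Simulation of 1,500 trials per setting, with intercepts set so that the marginal rates are 90/40/40%. Entries are the percentage of trials with p < 0.05.

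| OR per SD | χ², median split | χ², tertiles | *t* test, uncut, no arm term | Firth logistic, uncut, with arm |
|---|---|---|---|---|
| 1.0 (no effect) | 4.8 | 5.2 | 4.6 | 5.0 |
| 2.0 | 23.9 | 20.7 | 34.3 | 40.1 |
| 2.5 | 33.7 | 32.7 | 51.9 | 60.2 |
| 3.0 | 42.3 | 41.2 | 62.1 | 72.6 |

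- Loss from cutting (uncut *t* test minus median split): 10.4, 18.2 and 19.8 points.
- Further gain with arm in the model: 5.8, 8.3 and 10.5 points.
- Total: 16.2, 26.5 and 30.3 points.
- Tertiles do no better than a median split.

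**Sensitivity to sample size and effect.** A separate simulation compared the median-split χ² test with an ordinary likelihood-ratio test of the uncut variable with arm in the model.

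| Log OR per SD (OR) | 45 analysed: χ² vs model | 39 analysed: χ² vs model |
|---|---|---|
| 0.5 (1.65) | 15.7 vs 31.3 | 15.0 vs 27.7 |
| 0.8 (2.23) | 29.3 vs 58.0 | 29.0 vs 55.2 |
| 1.0 (2.72) | 41.7 vs 73.4 | 38.9 vs 69.0 |

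The loss is about 13 to 32 points over these settings. With no effect, the ordinary likelihood-ratio test rejected in 6.1% (45) and 5.4% (39) of trials, a reason to prefer a small-sample method.

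**Binary variable.** For a variable such as sex (two-thirds to one-third split assumed, 45 analysed), nothing is lost to cutting. χ² against the arm-adjusted likelihood-ratio test: 23.3% vs 32.5% at OR 3 (9 points), and 50.3% vs 64.6% at OR 6 (14 points).

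**Tested within each arm instead.** Among 15 controls, 15 × 0.10 = 1.5 are expected not to be constipated. A median split halves this to 0.75 per cell, far too few for a χ² approximation.

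**The case against.** The strongest reply is that a journal article condenses the plan, that covariate models and cut-points belong in an analysis plan, and that the abstract already lets the test depend on variable type. This stands for the missing cut-points taken alone. It does not remove the point, because the article goes further and names the method for this analysis. Its *t* and rank-based tests are assigned to the secondary variable.

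A reader might also infer more than the article supports:

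- **That the arms are pooled.** The article does not say so; it defines the main variable for each group. What is certain is that a two-way χ² test adjusts for nothing, and the within-arm reading fares worse in the control arm.
- **That all numeric measures are forced into categories.** This is certain only for age. The IPAQ may be used as levels. The CVE-20 and Bristol scale are outcomes in Table 1, and nowhere is either named as a predictor. χ² can handle sex, previous conditions and the habit-change question without any cutting.
- **That activity measured after the intervention would be related to constipation, mixing in the effect of arm.** The article does not say which IPAQ time point would be used, and a T0 value exists.
- **That 16 to 30 points is a property of the plan.** It follows from an assumed effect, a median split and a data model of the same form as the recommended analysis, which favours that analysis.

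Finally, the remedy is no cure for a small trial: at an odds ratio of 2 the adjusted model still has only about 40% power.

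**Conclusion.** The point holds as a low-cost improvement to an exploratory analysis. The stated method requires age to be cut into unspecified categories and leaves arm unadjusted. At an assumed odds ratio of 2 to 3 per standard deviation with 42 evaluable participants, a median-split χ² test gives up about 10 to 20 points of power from cutting and about 16 to 30 in total. For an already binary variable the cost is about 9 to 14 points, at assumed odds ratios of 3 to 6, and comes only from the missing adjustment.

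None of this touches the primary between-arm comparison or its sample size. Type I error is not the problem either: all the tests in the 42-participant simulation rejected close to 5% of the time when there was no effect. Weaker effects, other cut-points or a non-linear relation would change the figures.

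**What to change.** In the Statistical Analysis section, keep the χ² test and the relative risk for the between-arm comparison. For explanatory variables, replace the χ² test with wording such as: each baseline variable (Tpre or T0) will be related to constipation status, one at a time, in a small-sample (for example Firth-penalised) logistic model that includes arm; age, and the IPAQ if scored numerically, will enter uncut; sex, previous conditions and habit-change intention will enter as categories; the analysis is exploratory. State also how the IPAQ is scored.

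The cost is one or two sentences and a few lines of R on data already being collected. The downside is that results become odds ratios that assume a linear effect on the logit scale for numeric variables, which are less simple to present than a cross-table.

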The primary objective of this study is to evaluate the effectiveness of a structured rehabilitation program based on behavioral reeducation and abdominal massage therapy in reducing the prevalence of chronic constipation and the use of laxatives at 3, 6, and 12 months after the intervention. The secondary objectives are to assess changes in quality of life among participants and to evaluate whether the observed effects are sustained over time.

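### The tests named for quality of life include no T0 adjustment and no visit term, which costs precision and leaves the sustained-effect objective without a direct estimate

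*Protocol article*

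**What the plan says.** The last paragraph of the Introduction gives the secondary objectives: "to assess changes in quality of life among participants and to evaluate whether the observed effects are sustained over time". The Objective paragraph of the abstract says the same in substance.

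Table 1 (Variables section) lists the "CVE-20 questionnaire" as the quality-of-life instrument, at T0, T3, T6 and T12. That is one score at the start of the intervention and three later ones.

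The Statistical Analysis section covers the secondary variable, described as continuous, in two sentences. Across arms, "ANOVA or the Kruskal-Wallis test will be used to determine differences between the 3 groups". For pairs, "To determine differences between pairs of groups, the Student *t* test or Mann-Whitney test will be used". The section does not name quality of life as that variable; this follows from the objectives. It does not say which visit is tested or whether the score is a follow-up value or a change from T0. It plans multiple imputation for missing data, assumed missing at random.

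The Sample and Randomization section plans 15 participants per group, allocated by simple randomisation.

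**The concern.** The objectives ask two longitudinal questions: how quality of life changes, and whether the effect lasts. The named tests compare groups on a single number per person. None carries a baseline covariate, a visit term or an arm-by-visit term.

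Two things are at stake.

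- **Precision.** With 15 per arm and no stratification, chance T0 differences between two arms have a standard deviation of √(2/15) = 0.37 SD, so a gap above 0.5 SD arises in about 17% of pairwise comparisons. Adjusting for T0 removes the part of that noise that T0 predicts. The Sample and Randomization section says the trial should yield effect sizes for planning larger trials, so precision is part of its purpose.
- **The durability question.** Separate group comparisons at each visit do not estimate how the effect at a later visit differs from the effect at T3.

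**Working it through.** **The plan's own figure.** The only sample-size calculation is for the binary main outcome. It assumes that "approximately 90% of patients in the control group would remain constipated at 3 months", against 40% in the intervention groups, with 80% power and two-sided 5%. With pooled variance and mean proportion 0.65:

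n = [1.96 × √(2 × 0.65 × 0.35) + 0.842 × √(0.90 × 0.10 + 0.40 × 0.60)]² / 0.50² = (1.322 + 0.483)² / 0.25 ≈ 13.0 per group.

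Dividing by 0.90 for dropout gives about 14.5, hence 15. The stated figure is reproduced, but it says nothing about quality of life. The article gives no CVE-20 standard deviation, target difference or correlation.

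**Inputs for the precision check.** n = 15 per arm is from the article. The correlation r between T0 and a follow-up score is an assumption, taken as 0.3 to 0.7. Equal standard deviations at T0 and follow-up are also assumed, and the one degree of freedom spent on the T0 slope is ignored.

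**Variance of a pairwise comparison, relative to follow-up scores alone.**

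- Follow-up score: 1
- Change score: 2(1 − r)
- T0-adjusted (ANCOVA): 1 − r²

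The SE ratio of adjusted to follow-up is √(1 − r²). The ratio of adjusted to change is √[(1 − r²) / (2(1 − r))] = √[(1 + r)/2].

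| r | Change-score factor | Adjusted factor | SE fall vs follow-up | SE fall vs change | Equivalent n vs follow-up | Equivalent n vs change |
|---|---|---|---|---|---|---|
| 0.3 | 1.40 | 0.91 | 1 − 0.954 = 5% | 1 − 0.806 = 19% | 15/0.91 = 16.5 | 15/0.65 = 23.1 |
| 0.5 | 1.00 | 0.75 | 1 − 0.866 = 13% | 1 − 0.866 = 13% | 15/0.75 = 20 | 15/0.75 = 20 |
| 0.7 | 0.60 | 0.51 | 1 − 0.714 = 29% | 1 − 0.922 = 8% | 15/0.51 = 29.4 | 15/0.85 = 17.6 |

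The two comparisons run in opposite directions. Where r is low, follow-up scores lose little and change scores lose a lot; where r is high, the reverse holds. The adjusted analysis is better than both throughout the range.

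**Power, for illustration.** For an assumed true difference of 0.8 SD, a pairwise two-sided 5% test and 15 per arm:

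| r | Follow-up score | Change score | T0-adjusted |
|---|---|---|---|
| 0.3 | 56.2% | 43.2% | 60.2% |
| 0.5 | 56.2% | 56.2% | 68.5% |
| 0.7 | 56.2% | 77.9% | 84.2% |

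**The sustained-effect objective.** What is wanted is (arm − control at a later visit) − (arm − control at T3). No test named in the Statistical Analysis section yields it. If T3 and the later visit also correlate at r, its SE is √[2(1 − r) × 2/15] SD: 0.43 SD at r = 0.3 and 0.28 SD at r = 0.7. The 95% CI half-width is then about 1.96 × 0.43 ≈ 0.85 SD to 1.96 × 0.28 ≈ 0.55 SD. The contrast can be estimated, but imprecisely.

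**The case against.** **Which score is tested.** A reader might infer that only follow-up scores are compared and T0 is ignored. The article does not say so. The objective speaks of changes, so a t test or ANOVA on change from T0 is a natural reading, and it would use T0. This stands, and it means the 29% fall in SE (about 29 per arm) cannot be the headline: at r = 0.7 against change scores the fall is about 8%, equivalent to 17.6 per arm. It does not remove the point, because a change score is also less precise than adjustment across the range and still brings no visit term.

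**Detail left to an analysis plan.** A condensed article may leave covariates and visit handling to a fuller plan. That is fair as to silence on detail. But the article does name the tests for this outcome, and a T0-adjusted repeated-measures model would replace them, not fill them in.

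**Durability.** A reader might infer that durability will be judged from significance at one visit and non-significance at another. Nothing in the article says that. Group comparisons with 95% CIs at the later visits would show whether an effect is present then, which is one legitimate meaning of sustained. What remains is that the difference in effect between visits has no named estimate.

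**Validity.** Chance T0 imbalance under randomisation is random error already reflected in the CI. This stands in full: the loss is one of efficiency, in a secondary outcome.

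**Conclusion.** The point holds in a limited form. The analysis named for quality of life has no T0 adjustment and no visit term, and the score to be tested is not stated. Against a T0-adjusted analysis the standard error is needlessly large under either reading. For an assumed r of 0.3 to 0.7, the avoidable part is about 5% to 29% if follow-up scores are tested and about 19% to 8% if change scores are. These figures rest on the assumed correlation and on equal standard deviations, neither of which the article gives; at the favourable end for each score the gain is modest.

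The randomised comparison is not biased. The objective about effects lasting over time has no direct estimate among the named analyses. The change should be made because it improves the trial's answer at almost no cost, not because the existing tests are invalid.

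**What to change.** For CVE-20, replace the ANOVA/Kruskal-Wallis and t/Mann-Whitney tests with one linear mixed model of the follow-up scores, with terms for arm, visit, arm-by-visit, T0 CVE-20 and centre.

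- **Report** each intervention arm against control at each visit with a 95% CI. Report the later-minus-T3 difference in effect with its CI as the sustainability estimate, and state that a non-significant difference does not prove persistence.
- **Visits.** Include T3 and T6, and T12 if it is collected in all arms. The BI Group and BIM Group sections schedule follow-up at 3 and 6 months only, while the Control Group, Progress and Variables sections include 12 months. These passages must be reconciled first.
- **T0.** Apply the covariate in the same way in all arms. A rule tied to the first session cannot be applied person by person, since controls have none.
- **Missing data.** State how the model fits with the planned multiple imputation, for example whether imputation covers only missing T0 scores or the follow-up scores as well.

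The cost is analysis wording only. No new data or visits are needed, since the scores are already scheduled. The Progress section has data collection running to April 2026, so the wording is best settled before the results are analysed.

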### Intervention

#### BI Group

The behavioral education sessions are structured into two 60-minute workshops delivered in a progressive format. Session 1 focuses on understanding the physiology of defecation, the Rome IV diagnostic criteria, and bowel habits. Session 2 addresses lifestyle-related components, including dietary fiber and hydration guidelines, physical activity recommendations, stress management, optimal defecation posture, and the rational use of laxatives. The sessions are delivered by a multidisciplinary team (nurse, physician, physiotherapist, nutritionist, and psychologist) using multimedia presentations and printed handouts. Participants are encouraged to set personal bowel health goals. Questions and doubts raised during the first session will be discussed and resolved in the second session, ensuring continuity of learning and participant engagement.

The Bristol scale, Rome IV criteria, CVE-20 quality of life questionnaire, and International Physical Activity Questionnaire (IPAQ) [11,29-31] will be explained, and a calendar will be given to the patients to mark when they take any laxatives. Once the information sessions are complete, follow-ups will be scheduled 3 and 6 months later.

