#### BIM Group

The BIM group will receive the same intervention as the BI group, and the group will also participate in two 30-minute sessions with the physiotherapist to learn how to perform abdominal massage. In these sessions, the technique will be explained and an explanatory leaflet will be given to the participants so that they can do the massage independently at home.

The abdominal massage protocol follows a standardized clockwise technique that mirrors the path of the colon. The massage begins in the right lower quadrant (ascending colon), progresses to the upper abdomen (transverse colon), and concludes in the left lower quadrant (descending colon). Techniques include gentle effleurage, deep circular kneading, and vibration movements, applied in a slow, consistent rhythm. Each session lasts approximately 30 minutes. Participants are instructed to perform the massage once daily, preferably 20 to 30 minutes after a main meal, in a supine position with knees slightly flexed. The physiotherapist demonstrates the technique and provides a printed visual guide for home practice. The therapist will verify that participants have correctly learned the abdominal massage technique and are able to perform it independently.

To support adherence to the abdominal massage protocol, participants will be provided with a daily self-recording calendar to note each time they perform the massage at home. This calendar will be reviewed at follow-up visits. In addition, weekly SMS reminders will be sent to participants in the BIM group, encouraging them to maintain the daily routine and reinforcing key points of the technique.

Once these sessions are finished, follow-up sessions will be scheduled at 3 and 6 months. Participants will complete the questionnaires again and return the calendar, with marks showing when laxatives were used and massages performed.

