#### Control Group

The control group will receive the usual care in their primary care center and will be asked to complete the Bristol scale, Rome IV criteria, CVE-20 quality of life questionnaire, and IPAQ [11,29,30] at the beginning of the study and after 3, 6, and 12 months. They will also be given the calendar to mark when they take laxatives. This calendar will be collected after 3 months.

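### The trial's only claimed blind, one researcher blinded for data entry and analysis, is not secured as written, because the BIM calendars show the arm

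*Protocol article*

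**What the plan says.** All references are to the protocol article.

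- **Participants.** Statistical Analysis: "Due to the nature of the intervention, participant blinding is not feasible".
- **The blind that is claimed.** Same section: "data entry and statistical analysis will be performed by a researcher who is blinded to group allocation". Its stated benefit: "This approach ensures objectivity in the interpretation of results, particularly for subjective outcome measures". No other blind is claimed. The sealed envelopes under Sample and Randomization conceal allocation before assignment and do not bear on data handling afterwards.
- **BIM calendar.** At follow-up, BIM participants complete the questionnaires again and "return the calendar, with marks showing when laxatives were used and massages performed". The abstract's Methods paragraph likewise describes follow-up "using the same instruments and a self-recorded calendar of laxative use and massage application".
- **BI calendar.** Laxatives only: "a calendar will be given to the patients to mark when they take any laxatives".
- **Control calendar.** Laxatives only: "They will also be given the calendar to mark when they take laxatives". On timing: "This calendar will be collected after 3 months".
- **Table 1 (Variables).** The laxative calendar is listed at T3, T6 and T12, with no split by arm. Massage is not listed as a variable.

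**The concern.** The article makes a positive claim about blinding and then describes a source form that works against it. The laxative calendar has to be entered: reducing laxative use is part of the primary objective in the Introduction, and the calendar is the only instrument for it in Table 1. In one arm that form also carries a record of the treatment received.

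The role covers both entry and analysis, so the knowledge does not stay with the calendar. In the BIM Group section, questionnaires and calendar come in at the same follow-up. Someone who has seen massage marks against an ID could recognise that ID on the participant's Rome IV, Bristol, CVE-20 and IPAQ forms. Data entry is also where paper ambiguities are settled, such as whether a blank calendar day means no laxative or no record. The article states in advance that BIM is expected to do best (Principal Anticipated Findings).

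At stake is whether the final report can truthfully say that data entry and analysis were blinded, in a trial whose outcomes are self-reported by participants who know their arm.

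**Working it through.** The blinding claim contains no figure to recompute. The check is a comparison of what each form shows, plus the weight of one participant.

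**Step 1. The planned arm size.** Sample and Randomization gives 90% versus 40% still constipated, 80% power, two-sided 5%, 10% dropout, and 15 per group. By the arcsine formula:

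- h = 2·arcsin(√0.90) − 2·arcsin(√0.40) = 2.498 − 1.369 = 1.129
- n = 2·[(1.960 + 0.842)/1.129]² ≈ 12.3, rounded up to 13
- 13/(1 − 0.10) = 14.4, rounded up to 15

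This matches the stated 15. The pooled normal formula gives 14, inflated to 16, so 15 is a reasonable basis for what follows.

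**Step 2. What each form shows.**

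| Form | BIM | BI | Control | Shows the arm by content? |
|---|---|---|---|---|
| Calendar | laxative and massage marks | laxative marks | laxative marks | Yes for BIM; BI and control look alike |
| Rome IV, Bristol, CVE-20, IPAQ | same instruments | same instruments | same instruments | No |

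**Step 3. How many are identifiable by content.** The 15 planned BIM participants: 15/45 = one third.

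**Step 4. Is timing a second cue?** The Control Group section has the calendar collected after 3 months. Table 1 has the laxative calendar at T3, T6 and T12 for everyone. The two do not agree. If the Control Group section is followed and intervention calendars run longer, later calendars would separate control from BI. If Table 1 is followed, they would not. The follow-up visits show the same kind of mismatch: 3 and 6 months in the BI and BIM sections, 3, 6 and 12 months in the Control Group section, and all three for everyone in Table 1.

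**Step 5. Weight of one participant.** 1/15 = 6.7 percentage points on an arm's constipation rate, and 2/15 = 13.3 points, against a planned difference of 90 − 40 = 50 points. This says how much one reclassified participant counts. It does not estimate bias, because the article gives no rate of ambiguous forms.

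**The case against.** The strongest reply has four parts.

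1. **Masking or transcription may exist in documents not shown.** The article does not say that the blinded researcher keys raw calendars. Calendars are reviewed at follow-up visits, so other staff handle them first, and massage is not a Table 1 variable. The BIM Group section also introduces a daily massage calendar, which might be thought a separate sheet. This stands in part: a reader might infer that the blind cannot hold at all, and the text does not support that. But the same section ends with a single returned calendar carrying both kinds of mark, and data entry is assigned without exception to the blinded researcher. That is a stated property at odds with a stated procedure, which is more than missing detail.

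2. **BI and control are not distinguishable.** A reader might infer that control calendars stop at 3 months and that all 45 participants are therefore identifiable. This is not established. Table 1 contradicts it, the Control Group section does not say that no later calendar is issued, and the BI Group section gives no return date for its calendar. What remains is an inconsistency to reconcile.

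3. **The main variable is on a different form.** Rome IV forms do not show the arm, and the main analysis is a fixed chi-square test. The choice between parametric and rank tests concerns the continuous secondary variable, and its rule may sit in an analysis plan not shown. This stands. The main variable is reached only indirectly, by linking IDs, and 6.7 points must not be read as a bias.

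4. **Self-report by unblinded participants matters more.** Probably so. It does not justify claiming a blind that the procedure leaves open, and it is a further reason why a data-entry blind, even if intact, would not by itself ensure objectivity for subjective measures.

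**Conclusion.** The concern holds in a limited form. The one blind the article claims is not secured as written: BIM calendars identify the 15 planned BIM participants, one third of the sample, to whoever enters them, and the same person may link those IDs to other forms and then carries out the analysis. Whether control can also be told from BI is open until the Control Group section and Table 1 are reconciled.

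This rests on three assumptions: that the researcher named in Statistical Analysis enters the calendars, as the text implies; that no masking step is in place; and that arms reach the planned size (simple randomization may give somewhat different numbers).

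The size of any resulting bias cannot be estimated from the document. The results would remain usable, but the report would claim a protection that the described procedure does not provide. The remedy is cheap, so the change should be made.

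**What to change.** - **BIM Group:** record massage on a sheet separate from the laxative calendar.
- **BI, BIM and Control Group sections, and Table 1:** use the same laxative sheet in all three arms, with an ID code only, and reconcile the sections to one set of collection dates.
- **Statistical Analysis:** state that massage sheets are kept from the data-entry researcher until the Rome IV, Bristol, CVE-20, IPAQ and laxative data are entered and locked, and that the analyst works with arms coded A/B/C until the main analysis has been run.
- **Combined calendars already returned:** mask the massage marks before entry, or have existing staff outside data entry and analysis copy the laxative marks verbatim, leaving blanks blank. The treating physiotherapist should not do this, since it would pass the judgement on unclear days to an unblinded person who delivered the intervention.
- **If none of this is done:** remove the statements that data entry is blinded and that objectivity is thereby ensured.

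**Cost:** one extra sheet for BIM participants, a rule on the order of entry, and some protocol wording. Massage data become available later, and some returned forms need masking or copying. Enrollment closed in August 2025 and data collection is expected to run to April 2026 (Progress), so new sheets would reach only the remaining follow-up. No added staff or visits are needed.
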